## Abstract

**Background:**

Transcranial alternating current stimulation (tACS) has proven to be an effective treatment for improving cognition, a crucial factor in motor learning. However, current studies are predominantly focused on the motor cortex, and the potential brain mechanisms responsible for the therapeutic effects are still unclear. Given the interconnected nature of motor learning within the brain network, we have proposed a novel approach known as multi-target tACS. This study aims to ascertain whether multi-target tACS is more effective than single-target stimulation in stroke patients and to further explore the potential underlying brain mechanisms by using techniques such as transcranial magnetic stimulation (TMS) and magnetic resonance imaging (MRI).

**Methods:**

This study employs a double-blind, sham-controlled, randomized controlled trial design with a 2-week intervention period. Both participants and outcome assessors will remain unaware of treatment allocation throughout the study. Thirty-nine stroke patients will be recruited and randomized into three distinct groups, including the sham tACS group (SS group), the single-target tACS group (ST group), and the multi-target tACS group (MT group), at a 1:1:1 ratio. The primary outcomes are series reaction time tests (SRTTs) combined with electroencephalograms (EEGs). The secondary outcomes include motor evoked potential (MEP), central motor conduction time (CMCT), short interval intracortical inhibition (SICI), intracortical facilitation (ICF), magnetic resonance imaging (MRI), Box and Block Test (BBT), and blood sample RNA sequencing. The tACS interventions for all three groups will be administered over a 2-week period, with outcome assessments conducted at baseline (T0) and 1 day (T1), 7 days (T2), and 14 days (T3) of the intervention phase.

**Discussion:**

The study’s findings will determine the potential of 40-Hz tACS to improve motor learning in stroke patients. Additionally, it will compare the effectiveness of multi-target and single-target approaches, shedding light on their respective improvement effects. Through the utilization of techniques such as TMS and MRI, the study aims to uncover the underlying brain mechanisms responsible for the therapeutic impact. Furthermore, the intervention has the potential to facilitate motor learning efficiency, thereby contributing to the advancement of future stroke rehabilitation treatment.

**Trial registration:**

Chinese Clinical Trial Registry ChiCTR2300073465. Registered on 11 July 2023.

## Administrative information

Note: the numbers in curly brackets in this protocol refer to SPIRIT checklist item numbers. The order of the items has been modified to group similar items (see http://www.equator-network.org/reporting-guidelines/spirit-2013-statement-defining-standard-protocol-items-for-clinical-trials/).

## Introduction

### Background and rationale {6a}

Motor learning refers to the acquisition and solidification of a new motor skill, which plays an important role in rehabilitation activities [1]. The process of motor learning involves multiple brain regions, accompanied by changes in synaptic plasticity that can improve motor dysfunction caused by neurological damage, such as stroke [2]. In fact, the reacquisition of motor skills via motor learning holds the utmost significance in the recovery process of poststroke hemiparesis [3]. Therefore, the quest for efficacious tools and treatments to enhance motor learning after stroke becomes imperative.

Neural oscillations are rhythmic electric processes of neuron groups in the central nervous system that include five frequency bands: delta (δ, < 4 Hz), theta (θ, 4–7 Hz), alpha (α, 8–12 Hz), beta (β, 13–30 Hz), and gamma (γ, 30–100 Hz). In particular, γ oscillations are considered to emerge by activation of reciprocally connected excitatory pyramidal neurons and inhibitory interneurons and control the connectivity between different brain regions, which is crucial for perception, movement, memory, and emotion [4]. Studies show that γ oscillations, approximately 40 Hz, have been recorded during movement preparation during both externally triggered and self-paced hand movements [5], which means that γ oscillations are always present during movement onset and execution [6] and reflect the integration of visual, proprioceptive, and somatosensory information with ongoing motor activity.

Recent studies have shown that noninvasive brain stimulation (NIBS) techniques, such as transcranial alternating current stimulation (tACS), have emerged as potent tools to induce neural oscillations in the brain network. tACS can improve motor performance differentially by the injection of sinusoidal currents to modulate cortical excitability and brain electrical activity [7]. Compared to transcranial magnetic stimulation (TMS), tACS devices are inexpensive and convenient to use and have smaller electrode pads that can achieve multi-target stimulation in the brain. Furthermore, tACS can set different stimulation frequencies to induce different neural oscillation bands compared to transcranial direct current stimulation (tDCS).

A growing number of studies attest to the benefits of tACS in motor learning [8], motor skills enhancement [9], and cognitive augmentation [10]. Numerous studies concur that 40 Hz tACS significantly enhances cognitive function in healthy people and individuals with Alzheimer’s disease (AD) [11–16]. In addition, Hopfinger et al. revealed that 40-Hz tACS facilitates endogenous attention in mice with Alzheimer’s disease, highlighting the pivotal role of slow gamma oscillations (induced by 40 Hz stimulation) in attentional disengagement and reorientation [17]. The above studies reveal that the improvement of cognitive function could be achieved by 40-Hz tACS in both humans and mice. It is worth noting that the newest research affirms a significant correlation between cognitive ability and motor learning function in the elderly [18]. However, most current tACS studies focus on a single cortical stimulation area related to movement or cognition (single target), which neglects an important point of neural function regulated by brain networks [19–21]. Direct evidence regarding the impact and brain mechanism of multi-target 40 Hz tACS on the motor learning of stroke patients is currently lacking.

Many clinical studies have confirmed the functional connectivity between the primary motor cortex (M1), primary sensory cortex (S1), and dorsolateral prefrontal cortex (DLPFC). The coactivation of M1 and S1 and DLPFC in planning, execution, and control of movement has been well established [22–24]. In addition to the three brain regions mentioned above, recent studies have shown that cerebellar (CB) tACS can lead to improved cortical excitability and motor behavior [25], which affects balance and gait, limb movement, oculomotor control, and cognition.

## Objectives {7}

Based on the above theory, we proposed that simultaneous stimulation of M1, S1, DLPFC, and CB (multi-target tACS) can be more effective than single-target stimulation due to the enhancement of motor learning-related brain network interactions. With appropriate control experiments, the potential underlying brain mechanism will be studied by behavioral tasks and assessments of scales, EEG, MRI, and TMS. Furthermore, we will perform RNA sequencing analysis on the blood samples of the stroke participants before and after the intervention to further analyze the changes in neuroinflammatory factors, nerve growth factors, and synaptic plasticity genes. The objectives of this study are to explore the effects of multi-target tACS on motor learning function in stroke patients and explore the underlying brain mechanism.

## Trial design {8}

This study will be a randomized controlled trial utilizing a parallel-group design. A total of 39 stroke patients will be assigned to three groups: the sham tACS group (SS group), single-target tACS group (ST group), and multi-target tACS group (MT group) at a 1:1:1 ratio as determined by a simple random sampling process. The comprehensive study flowchart is depicted in Fig. 1, while the study schedule is outlined in Table 1. The protocol was approved by the Ethics Committee of Shanghai Seventh People’s Hospital (2023-7th-HIRB-043) and will be conducted in accordance with the ethical standards of the Declaration of Helsinki. The protocol has been registered in the Chinese Clinical Trial Registry (ChiCTR2300073465) and used the SPIRIT reporting guidelines [26]. Prior to participating in the experiment, patients will be required to provide informed consent.

**Fig. 1 Fig1:**
[figure not shown]
Comprehensive study flowchart of the protocol

**Table 1 Tab1:**
[figure not shown]
Schedule of enrollment, intervention, and assessments

“√” means things will be done. *SRTT* series reaction time test, *EEG* electroencephalogram, *BBT* Box and Block Test, *MEP* motor evoked potential, *CMCT* central motor conduction time, *SICI* short interval intracortical inhibition, *ICF* intracortical facilitation, *MRI* magnetic resonance imaging

## Methods: participants, interventions, and outcomes

### Study setting {9}

Recruitment of stroke patients, assessment of scales and equipment, and electrical stimulation interventions will all be conducted at the Shanghai Seventh People’s Hospital in China.

### Eligibility criteria {10}

#### Inclusion criteria

Age between 40 and 75 years, possessing normal or corrected-to-normal vision.Right-handedness, as indicated by a score greater than 40 points on the Edinburgh Handedness Scale [27].Experienced a single (first ever), unilateral stroke (ischemic or intracerebral hemorrhagic) within the timeframe of 2 weeks to 6 months from onset.Exhibiting clear consciousness and absence of mental disorders, with a score exceeding 23 points on the Mini-Mental State Examination (MMSE) [28].Demonstrating a willingness to cooperate in the research and providing voluntary consent by signing the informed consent form.Presenting an upper limb with a Brunnstrom scale grade ranging from III to V.

#### Exclusion criteria

Presence of contradictions for tACS, TMS, or MRI, such as implantable electronic device or compromised skin in the stimulation area resulting from damage or hyperalgesia.Diagnosis of any other neurological conditions, including depression, severe language comprehension deficits, unilateral spatial neglect, epilepsy, upper-limb apraxia, etc.Proficiency in demanding finger movements, such as piano players, professional game players, and individuals with prior experience in sequential response time testing (SRTT).Ongoing participation in concurrent clinical studies.Identifications of additional reasons, as deemed by researchers, rendering the participant unsuitable for inclusion in the experiment.Inability to comprehend or provide a signature on the informed consent form.

### Who will take informed consent? {26a}

The informed consent will be conducted by experienced neurologists and signed by two sides (blinded physicians and stroke patients). The potential participant has sufficient time to read the full text of the informed consent form, and neurologists will introduce the details of the contents of the informed consent form to them. Finally, the patient will decide whether to participate in the study by themselves. All participants will sign informed consent before the study, and all methods will be performed in accordance with the Declaration of Helsinki.

### Additional consent provisions for collection and use of participant data and biological specimens {26b}

After the patient signs informed consent, blood will be sampled by venipuncture of the elbow from participants. The entire blood sampling process is operated by a professional neurology nurse and extracts about 2 ml.

### Interventions

#### Explanation for the choice of comparators {6b}

The study included one sham and two active stimulation interventions delivered to three parallel groups.

In the SS group, a “pseudo stimulus” button will be discreetly activated, providing a semblance of stimulation to the subject without their awareness. For the ST group, the current channel will solely target M1, while the remaining three brain areas will receive pseudo stimulation, akin to the SS group. In the MT group, all four channels will be activated simultaneously. The entire process of electrical stimulation intervention will be closely supervised by a proficient clinical operator in conjunction with emergency personnel. Sham stimulation enables a placebo comparator to the active conditions.

#### Intervention description {11a}

The multi-target tACS will be performed using a multichannel transcranial electrical stimulator (YingChi, Shenzhen). All participants will undergo a daily 20-min tACS session over a 2-week period. A skilled physiotherapist will conduct the sham tACS, single-target tACS, or multi-target tACS intervention on patients under the standardized condition. The tACS session will be delivered to the cortex via surface sponge electrodes (5 × 7 cm) soaked in 0.9% NaCl, which will be employed and secured in place using elastic gauze. Based on previous experimental research [29], the following stimulation parameters will be employed: a stimulating intensity of 1 mA peak to peak and a stimulation frequency of 40 Hz. For electrode placement, participants will receive a total of 4 pairs of electrode pads. The anodes will be placed in the M1, S1, DLPFC, and CB in alignment with the affected brain area, while cathodes will be placed in the contralateral brain area for each corresponding electrode [30].

#### Criteria for discontinuing or modifying allocated interventions {11b}

There are no anticipated problems that are detrimental to the participant.

#### Strategies to improve adherence to interventions {11c}

To ensure the protocol adherence of the intervention and assessment, all the neurologists, physiotherapists, and nurses involved in the research project will be trained according to the recommended guidelines and protocols.

#### Relevant concomitant care permitted or prohibited during the trial {11d}

During the study, the stroke patients will be able to continue their daily treatment plan at the hospital as usual.

#### Provisions for post-trial care {30}

There is no anticipated harm for tACS intervention. However, participants who feel uncomfortable, such as skin itching, will be evaluated by the neurologist for further necessary treatment.

### Outcomes {12}

Assessments will be conducted by physiotherapists blinded to the group allocation at various designated time points, as outlined in Table 1. Additionally, a comprehensive questionnaire (administered during week 0) will capture baseline information, including age, gender, symptoms, disease severity, duration, prior treatment, and medication history, which will be recorded using a questionnaire. Additionally, any encountered side effects throughout the course of the study will be promptly documented and reported in real time.

#### Primary outcomes

##### Series reaction time test task (SRTT)

The series reaction time task (SRTT) is the most commonly used method to assess motor learning function. The combination of SRTT and EEG is an important method for investigating the effects and brain mechanisms of motor learning [31]. We will use software (Deary-Liewald, UK) [32] to evaluate the changes in motor learning pre- and post-tACS intervention. Prior to commencing the SRTT, participants will be seated in front of a 15.6-in. computer screen with their hemiplegic-side hand resting on the keyboard. The mapping of fingers to the correspondence numbers is as follows: index finger = V, middle finger = C, ring finger = X, and little finger = Z. Four white squares will be positioned approximately in the center of a computer screen, contrasted against a blue background (refer to Fig. 2). The arrangement of the keyboard keys mirrors the layout of the squares on the screen: the “V” key aligns with the far-left square, “X” key with the second-left square, “C” key with the second-right square, and “Z” key with the far-right square. The task involves responding to the appearance of a diagonal cross within each square by promptly using the corresponding keyboard key. Participants are required to execute this key as quickly as possible upon each cross’s appearance.

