**Fig. 2 Fig2:**
[figure not shown]
Screenshot of the SRTT software used in this study

The task includes 10 practice trials followed by 80 experiment trials, collectively lasting no more than 10 min for each participant. The interstimulus interval (measured in milliseconds, refers to the duration between a response and the subsequent appearance of a cross) will be randomly set within the range of 1000–3000 ms. The computer program will record the response time and the interstimulus interval for each trial [33].

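### The SRTT key map contradicts itself and its single finger map suits only a left hand, so the primary reaction time depends on affected side; no sequence-versus-random contrast is described

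*Protocol article*

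**What the plan says.** The section on the series reaction time test task, the first-named primary outcome, seats the participant "with their hemiplegic-side hand resting on the keyboard". It gives one finger assignment for everyone: "index finger = V, middle finger = C, ring finger = X, and little finger = Z". It then states a general principle, "The arrangement of the keyboard keys mirrors the layout of the squares on the screen", and spells it out: the V "key aligns with the far-left square, “X” key with the second-left square, “C” key with the second-right square", with Z for the far-right square.

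The inclusion criteria do not restrict the side of the lesion ("Experienced a single (first ever), unilateral stroke (ischemic or intracerebral hemorrhagic") and require "Right-handedness, as indicated by a score greater than 40 points on the Edinburgh Handedness Scale". The section on sequence generation stratifies by sex, age and Brunnstrom grade; affected side is not a factor.

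On trial structure, the text below Fig. 2 says: "The task includes 10 practice trials followed by 80 experiment trials, collectively lasting no more than 10 min for each participant". The interval between a response and the next cross "will be randomly set within the range of 1000–3000 ms". Response time and interval are recorded for each trial. The order in which the squares are used is not stated. The task is presented as a measure of change in motor learning.

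**The concern.** A choice reaction time depends heavily on how stimulus positions map to keys and fingers. If the written map is followed, every patient works with a scrambled correspondence, and those with a right hemiplegic hand must also reverse or cross their fingers. Part of the primary score then reflects which side is affected. That is noise in the comparison of arms, and it can fall unevenly in arms of 13.

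A second matter is what the score means. The trial asks about motor learning. As the task is described, nothing separates learning of a sequence from responding faster overall, so a positive result would be open to more than one interpretation.

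**Working it through.** No sample size, power or alpha figure in the article bears on this point, so there is no stated figure to reproduce. The check is a comparison of orders, followed by one probability.

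**Square-to-key map.** Assumption: a standard Latin keyboard, bottom row Z, X, C, V from left to right. Number the positions Z=0, X=1, C=2, V=3.

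| Squares, left to right | Keys | Key positions |
|---|---|---|
| As stated | V, X, C, Z | 3, 1, 2, 0 |
| Same order as keyboard | Z, X, C, V | 0, 1, 2, 3 |
| Reversed order | V, C, X, Z | 3, 2, 1, 0 |

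The stated map matches neither consistent reading of the claim that the keys mirror the squares. The outer pair is crossed and the inner pair is not.

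**Square-to-finger map.** Passing V, X, C, Z through the stated finger assignment gives index, ring, middle, little for the squares from left to right. That is the natural order of neither hand.

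**Finger-to-key map on its own.** Along Z, X, C, V the assigned fingers are little, ring, middle, index. That is a left hand, palm down. A right hand lies index, middle, ring, little, so it cannot take this assignment without reversing or crossing fingers. This holds whatever is done about the square map.

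**Link to affected side.** The tested hand is the hemiplegic one and either side is eligible. Because all participants are right-handed, side also decides whether the tested hand is the dominant one.

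**Chance imbalance.** The article gives no proportion of right-sided patients, so 50% is assumed first, with 39/3 = 13 per arm. Let D be the difference in right-sided counts between two given arms.

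- SD(D) = √(2 × 13 × 0.5 × 0.5) = 2.55.
- Exactly, D + 13 is Binomial(26, 0.5). So P(|D| ≤ 2) = (10,400,600 + 2 × 9,657,700 + 2 × 7,726,160) / 2²⁶ = 45,168,320 / 67,108,864 = 0.673.
- P(|D| ≥ 3) = 1 − 0.673 = 0.327, about one in three.
- At 30% or 70% right-sided, SD(D) = √(2 × 13 × 0.3 × 0.7) = 2.34. The same probability, summed exactly over two Binomial(13, 0.3) counts, is 0.283.

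These figures count patients. The article gives nothing from which to convert them into milliseconds or power.

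**Trial structure.** The description contains 10 practice trials, 80 experimental trials, a random interval, and two recorded quantities. It contains no repeating order, no random-order block and no difference between the two. Only the interval is called random; the order of squares is left open.

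**The case against.** The square map may be a slip in the writing. Exchanging X and C gives the reversed order, and exchanging V and Z gives the direct one. That is plausible, but the two corrections are different tasks and the text does not show which one the software runs. The finger map remains a left-hand map either way.

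A stable effect of side partly cancels, because the SRTT is taken at baseline and again later and analysed with repeated measures. Any imbalance under randomisation is chance, not systematic bias. Both points stand and limit the harm. What does not cancel is a side effect on the change itself, for example if an awkward map is learned at a different rate over repeated tests. That is possible, but the article gives no evidence for or against it.

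A reader might infer that no repeating sequence is run. The article does not say so. It calls the task a series reaction time task, its exclusion criteria refer to prior experience of sequential response time testing, and a condensed article may leave block lists to the full protocol. A reader might also infer that errors go unrecorded; the article lists response time and interval but does not say that nothing else is kept.

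Nor does natural recovery or task familiarity explain a difference between arms, since the sham arm shares both. What remains is narrower: whether a gain in an active arm is sequence learning, or general speeding and better hand function.

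**Conclusion.** The specification of the primary task is internally inconsistent and should be corrected. The square-to-key order contradicts the stated correspondence and suits neither hand. The single finger map suits only a left hand although either may be tested. Given a standard keyboard layout, this follows from the text alone.

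The consequence is extra between-patient variance tied to affected side, and possible chance imbalance: about a 33% chance that two given arms of 13 differ by 3 or more right-sided patients if half are right-sided, and about 28% at 30% or 70%. Within-patient change offsets part of it.

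It is tempting to count only right-hemiplegic patients as exposed to an incompatible map. That does not fit the text: taken literally, the square map is unnatural for all 39, and only the finger map divides patients by side.

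On construct validity, the supportable statement is that no sequence-versus-random contrast is described. It calls for confirmation by the sponsor and is not a demonstrated absence.

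**What to change.** Before the first patient:

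1. Check which square-to-key map the software uses and reconcile the text with it, so that the correspondence is spatially consistent.
2. Give separate finger maps for the left and the right hand.
3. Add affected side as a covariate in the primary SRTT analysis.
4. State the order of squares over the 80 trials. If a repeating sequence is used, describe it and the comparison that yields the learning score. If none is used, either embed a sequence-versus-random contrast or limit the conclusion to choice reaction time. If a contrast is added, say how it fits within 80 trials and how a sequence already met at one visit is handled at the next.

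Items 1 to 3 cost protocol wording, a check of the task set-up and one model term. Item 4 costs wording alone, unless a contrast is added; that may lengthen each test by a few minutes. No extra visit is needed. Responses collected under an inconsistent map cannot be repaired afterwards, so the timing matters.
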